### 2. Antiretroviral Therapy

Antiretroviral drugs will be managed according to good clinical practice. There will be no restrictions on access to antiretroviral therapy during the course of this study. The decision to initiate antiretroviral therapy should be made upon sound clinical evidence that doing so would be in the interest of the patient, their health and well-being.

Optimally, changes to antiretroviral therapy should be made at least 2 weeks following completion of IL-2 therapy and at least 2 weeks prior to commencement of the next cycle. The rationale for change in antiretroviral therapy will be noted clearly in the case report forms.

Patients receiving IL-2 therapy are not required to be on antiretrovirals during the time of IL-2 administrration under this protocol.

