# I. SYNOPSIS

This protocol describes a randomized, phase II study of subcutaneous interleukin-2 (IL-2) therapy in HIV disease. There are three primary objectives:

1. to demonstrate the safety and tolerance of IL-2 in the absence of concomittant antiretrovirals.

2. to demonstrate the immunological efficacy of IL-2 in the absence of concomittant antiretroviral therapy as defined by increases of CD4+ cell counts from baseline.

3. To assess the effects of IL-2 in the absence of concomittant antiretroviral therapy on plasma HIV RNA levels as defined by changes from baseline.

Approximately 36 patients with HIV infection, > 350 CD4+ cells/mm3 and no history of opportunistic infection will be required to complete the trial. Individuals never previously treated with antiretrovirals will be eligible to participate. Eligible patients will be randomly assigned to receive one of two treatment regimens:

A. No therapy (n=12)

B. Subcutaneous IL-2 at one of 2 doses, q12h x 5 days every 8 weeks (n=24)

Two different dose levels of IL-2 will be studied. The first group will receive 4.5 million units (MIU) q12h x 5 days every eight weeks. The second group will receive 7.5 MIU q12h x 5 days every eight weeks. Following the completion of this study, continued treatment for all patients will be made available through an additional protocol that will be based upon the results of the current study. It is anticipated that this additional study will be a phase III trial involving a total of 3700 patients worldwide.

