# V. STUDY DESIGN

### A. OVERVIEW

This is a phase II open label study of escalating doses of subcutaneous (SC) IL-2 alone versus no therapy in patients with HIV infection and a CD4+ lymphocyte count of at least 350 cells/mm3. This protocol is intended to define the safety and tolerability, immunological superiority and virological neutrality of IL-2 immunotherapy over no therapy.

There will be 3 treatment arms (1 control; 2 IL-2). Eligible patients will be randomized to receive no therapy or IL-2 therapy with two discreet doses of SC IL-2 (delivered for five days every eight weeks).

A total of 36 patients will be required to complete a minimum of three cycles of treatment. Of these patients, 12 will be allocated to receive no therapy and 24 patients will receive SC IL-2. A cycle is defined as 8 calendar weeks to include as necessary one five day period of SC IL-2 therapy.

Dosing with SC IL-2 will commence at doses of 4.5 MIU or 7.5 MIU twice daily (q12h) for 5 days every eight weeks. No patient will be treated with more than 7.5 MIU q12h x 5 days every eight weeks and no patient will commence a treatment cycle at a dose of less than 1.5 MIU q12h x 5 days every eight weeks.

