### C. Exclusion criteria

a) prior IL-2 therapy.

b) prior or current use of any approved or experimental antiretroviral drug.

c) concurrent malignancy other than mucocutaneous Kaposi sarcoma or malignancy treated within the past 5 years.

d) any concurrent or history of AIDS defining illness (CPCRA appendix B).

e) use of systemic corticosteroids, chemotherapy or experimental cytotoxic drugs within four weeks prior to study therapy.

f) use of any agent approved or experimental with clinically significant immunomodulatory effects.

g) any CNS abnormality that requires treatment with anti-seizure medication.

h) patients with current or historical CrohnÕs disease, psoriasis or other autoimmune/inflammatory diseases with potentially life threatening complications.

i) pregnant or lactating women.

j) occasional or habitual use of recreational drugs/alcohol that in the opinion of the principal investigator would affect patient safety and/or compliance.

k) patients with any serious psychiatric, medical and/or cognitive disturbance or illness that in the opinion of the principal investigator may affect safety, compliance or ability to provide written informed consent.

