### 3. Analysis of data

The final analysis will be conducted once all randomized patients have completed completed the study as described OR one year following initiation of the study. There will be no interim analyses of efficacy data for the purposes of early study termination.

a) Patient characteristics

Patient characteristics at baseline will be summarized by randomized treatment using appropriate summary measures. Patient characteristics to be summarized will include age, sex, baseline CD4+ cell count and virus load. There will be no formal comparisons of baseline characteristics performed.

b) Efficacy parameters

All efficacy data will be analyzed by the intent-to-treat principle. In particular, all doses of SC IL-2 used in the escalation phase will be included in the data from treated patients.

The change from baseline in CD4+ cell count and virus load will be summarized at each sampling time point. Formal analysis will compare the randomized treatments in terms of time-weighted changes from baseline using ANOVA methods, or equivalent non-parametric methods as appropriate.

c) Safety

Safety data will be summarized by treatment received for each time point.

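### The CD4+ and HIV-RNA objectives ask about IL-2 without antiretrovirals, but the only stated efficacy analysis is intent-to-treat with antiretrovirals freely available, so it estimates a treatment-policy effect

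*Protocol*

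**What the plan says.** **Objectives.** Synopsis objective 2 is "to demonstrate the immunological efficacy of IL-2 in the absence of concomittant antiretroviral therapy as defined by increases of CD4+ cell counts from baseline". Objective 3 is "To assess the effects of IL-2 in the absence of concomittant antiretroviral therapy on plasma HIV RNA levels as defined by changes from baseline". Section IV makes the comparison relative to patients given no therapy, and section V.A adds the aim of showing "immunological superiority and virological neutrality of IL-2 immunotherapy over no therapy".

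**Antiretrovirals at entry.** Section VI.C excludes "prior or current use of any approved or experimental antiretroviral drug".

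**Antiretrovirals on study.** Section VII.C.2 states: "There will be no restrictions on access to antiretroviral therapy during the course of this study". The condition is clinical judgement: "The decision to initiate antiretroviral therapy should be made upon sound clinical evidence that doing so would be in the interest of the patient". The timing advice is not binding: "Optimally, changes to antiretroviral therapy should be made at least 2 weeks following completion of IL-2 therapy", with a similar interval before the next cycle. Section VII.D.1 leaves need to be judged patient by patient. Section IX.A does not list an antiretroviral start as a reason to withdraw study therapy.

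**Analysis.** The primary endpoints in section VIII.E.1 are the time-weighted mean changes from baseline in CD4+ count and HIV-RNA. Section VIII.E.3 states: "All efficacy data will be analyzed by the intent-to-treat principle". The randomized groups are then compared by ANOVA or a non-parametric equivalent. Safety is handled differently and is summarized by treatment received. Sections VIII.E.1 to VIII.E.3 do not mention antiretroviral starts.

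**The concern.** The objectives and the analysis address different quantities. Using every value by randomized arm, whatever was started later, answers a legitimate strategy question. It does not isolate what IL-2 does while no antiretroviral is taken.

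Antiretrovirals act directly on both primary endpoints, so an imbalance in starts feeds into both comparisons:

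- **More starts among controls.** Control HIV-RNA falls and control CD4+ rises. IL-2 can look virologically harmful, and part of a real CD4+ gain is hidden.
- **More starts in the IL-2 arms.** A real rise in HIV-RNA on IL-2 is pulled down and the antiretroviral CD4+ gain is credited to IL-2. The trial could then report neutrality and efficacy that IL-2 alone did not produce.

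The second case matters more, because neutrality is a stated aim and the Synopsis links this trial to a planned phase III study of 3700 patients.

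Three features make unequal starts plausible. The trial is open label with an untreated control. Virology is more frequent in the IL-2 arms: Table 3 has it before each cycle, at day 29 of each cycle and at day 8 of the first, whereas Table 4 has controls sampled every 8 weeks. The background in section II also reports bursts of viremia at the end of IL-2 cycles and two- to three-fold rises at day 5, which could prompt starts among IL-2 patients.

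**Working it through.** **1. The plan's own figure.** Inputs from section VIII.E.2: SD 0.7 log, difference 0.7 log, 24 IL-2 and 12 control patients, two-sided 5%.

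- Standard error = 0.7 × √(1/12 + 1/24) = 0.247.
- Power = Φ(0.7/0.247 − 1.96) = Φ(0.868) = 81% (78.5% with the noncentral t).
- The CD4+ case (SD 150, difference 150) has the same ratio and the same power.

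The stated 80% reproduces. The sample size is not in error.

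**2. Precision for judging neutrality.** With 34 degrees of freedom the 95% confidence interval half-width is 2.03 × 0.247 = 0.50 log.

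**3. Weight of values after a start.** Controls are sampled at weeks 0, 8, 16 and 24 (Table 4). The protocol fixes no weighting rule, so trapezoidal weighting is assumed. The weights are 4/24, 8/24, 8/24 and 4/24. A start after the week 8 sample and before the week 16 sample affects the last two values, a share of (8 + 4)/24 = 0.5. This assumes the full fall is present by week 16.

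In the IL-2 arms (weeks 0, 4, 8, 12, 16, 20 and 24, ignoring day 8) the share is (4 + 4 + 4 + 2)/24 = 14/24 for a start just after week 8 and (4 + 4 + 2)/24 = 10/24 for one just after week 12. These lie either side of 0.5, so 0.5 is used throughout.

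**4. Shift in the between-arm HIV-RNA difference.** Shift = difference in start proportions × log fall × share. The start proportions and the 1.0 to 2.0 log fall are assumptions; the protocol gives neither.

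| Excess starts in one arm | Fall 1.0 log | Fall 2.0 log |
|---|---|---|
| 25 points | 0.25 × 1.0 × 0.5 = 0.125 | 0.25 × 2.0 × 0.5 = 0.25 |
| 50 points | 0.50 × 1.0 × 0.5 = 0.25 | 0.50 × 2.0 × 0.5 = 0.50 |
| 0 points | 0 | 0 |

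The largest shift is 0.50/0.7 = 71% of the design difference and about equal to the half-width in step 2.

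**5. Consequence for the test.** Take 25% starting in one arm and none in the other. With m = fall × share, the variance in the arm with starts is 0.49 + m² × 0.25 × 0.75.

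- *IL-2 truly neutral, excess among controls.* For a 1.0 log fall the SE is √(0.537/12 + 0.49/24) = 0.255, and the chance of p < 0.05 is 8%. For a 2.0 log fall it is 15%. The nominal rate is 5%.
- *IL-2 truly raises HIV-RNA by 0.7 log, excess in the IL-2 arms.* The expected observed difference is 0.575 log (1.0 log fall) or 0.45 log (2.0 log fall). Power falls from 81% to 63% or 40%.
- *Equal starts of 25% in each arm.* There is no shift in this illustration, where the true 0.7 log difference is preserved. Power is 77% to 67% because the starts add variance.

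**6. CD4+.** Assume a time-weighted antiretroviral gain of 50 to 100 cells/mm3 and 25 to 50 points more starts among controls. The 150-cell difference becomes 150 − 0.25 × 50 = 137.5 at best and 150 − 0.50 × 100 = 100 at worst. With SE = 150 × √(1/12 + 1/24) = 53, power is 74% and 47%.

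**The case against.** **The wording may only contrast with earlier trials.** Previous randomized IL-2 trials added IL-2 to antiretrovirals. Here antiretrovirals are excluded at entry and not required afterwards, and sections II and II.C describe IL-2 as a possible strategy for patients who do not wish to start antiretrovirals. A strategy question is properly answered by intent-to-treat. This stands as a defensible reading, and it is why intent-to-treat should remain primary. It does not remove the need to say which quantity is estimated, since the Synopsis wording invites the other reading.

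**It belongs in the statistical analysis plan.** A plan not shown may add supplementary analyses, and their absence from the protocol would not by itself be a finding. The point rests on the protocol's own objective and its own stated analysis, which do not match.

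**Starts may be rare.** Patients are asymptomatic, have at least 350 CD4+ cells/mm3, do not wish to start antiretrovirals, and control follow-up is about 24 weeks. This stands: nothing in the protocol supports any particular start rate.

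**Stronger readings that the documents do not support.** A reader might infer that the comparisons are bound to be biased; bias needs starts that differ by arm. A reader might infer that the protocol ties starts to CD4+ and viral load. It asks for sound clinical evidence and names neither, so that dependence is an inference. A reader might also extend the point to all three primary objectives, but safety is summarized by treatment received and falls outside the intent-to-treat rule.

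**Stopping at the start is itself selective.** Cutting follow-up at the first dose is informative, gives patients unequal averaging windows, and leaves a control who starts before week 8 with no scheduled post-baseline value. This stands, so such an analysis can only supplement intent-to-treat.

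**Conclusion.** The mismatch is real and lies within the protocol. The efficacy objectives are worded for IL-2 without antiretrovirals, while the stated analysis estimates the effect of assignment to IL-2 with antiretrovirals available as needed in every arm. The trial can still answer the second question as designed.

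The size of any distortion is unknown. Under the assumptions shown (25 to 50 points more starts in one arm between weeks 8 and 16, a 1.0 to 2.0 log fall, trapezoidal weighting) it is about 0.13 to 0.50 log against a 0.7 log design difference, in either direction. With few or equal starts it is small or nil. The main risk is a conclusion of virological neutrality that antiretroviral starts in the IL-2 arms helped to produce. This is a cheap improvement to the analysis wording.

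**What to change.** In section VIII.E.3:

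1. Keep intent-to-treat as the primary efficacy analysis and state that it estimates a treatment-policy effect: IL-2 with antiretrovirals as needed against antiretrovirals as needed.
2. Report antiretroviral starts by randomized arm, with their timing.
3. Pre-specify a supplementary analysis of the time-weighted change using values up to the first antiretroviral dose.
4. Because that truncation is informative, add a worst-rank sensitivity analysis that counts a start as an unfavourable outcome. It also retains patients who have no value before starting.
5. Claim an effect, or neutrality, of IL-2 without antiretrovirals only if these analyses agree.

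The cost is one or two extra analyses and a start date for the first antiretroviral; the case report form already takes the rationale for antiretroviral changes. The supplementary analysis will have shorter and possibly selected follow-up, and should be read with that in mind. Access to antiretrovirals and the sample size stay as they are.

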### D. CONCOMITANT THERAPY

### 1. Antiretroviral Therapy

Antiretroviral therapy is not a mandatory component of this study. Investigational teams will monitor patient performance at regular intervals to determine the needs of individual patients in terms of antiretroviral therapy

### 2. Antimicrobial Prophylaxis

Patients whose CD4+ cellcount falls to below 200 cells/mm3 should commence prophylaxis for *Pneumocystis carinii* pneumonia. In patients with a reduction in CD4+ cell count to less than 100 cells/mm3 and 50 cells/mm3 prophylaxis for *Mycobacterium* *avium* complex and Cytomegalovirus disease respectively, may be initiated. Patients with a history of recurrent Herpes simplex infection who are in receipt of suppressive therapy with acyclovir at commencement of study therapy may continue to receive prophylaxis.

### 3. Treatment of Intercurrent Illnesses

Patients who develop intercurrent illnesses during the trial may receive appropriate systemic therapy followed by appropriate suppressive therapy thereafter. Treatment with IL-2 may be delayed for the management of acute signs and symptoms of intercurrent illnesses as well as toxicities arising from antiretroviral therapy or IL-2. Generally the maximum interval between treatment cycles should not be extended by more than 11 calendar weeks.

### 4. Symptomatic Management During IL-2 Treatment

The use of symptomatic medications during treatment with IL-2 is encouraged. A list of appropriate interventions of this nature is presented in Appendix F.

# VIII. STUDY PROCEDURES

### A. General

Written informed consent must be obtained prior to any study specific tests or evaluations being performed. Additional laboratory tests to those identified in this protocol, necessary to assess patient safety may be performed at the discretion of the investigator. Any other tests should be approved by the appropriate Institutional Review Committee and presented to the potential participant in the informed consent.

Scheduled visits may be adjusted to accommodate holidays. Flexibility of scheduling will generally be at the discretion of the investigator who must determine that patient care and safety will not be compromised. Delay of treatment cycles by more than two weeks from scheduled dates is to be avoided.

### B. Pre-therapy (all patients)

All pre-therapy evaluations must be conducted within 30 days prior to randomization. There will be three pre-study visits required prior to commencement of IL-2 therapy. Patients randomized to receive IL-2 therapy should commence the first treatment cycle within 45 days of pre-therapy visit 1.

#### 1. Visit 1

- provision of written informed consent
- complete medical history and physical examination, weight, blood pressure, respiration rate and temperature (hereafter referred to as **vital signs**)
- chest X-ray and electrocardiogram (unless results are available from studies undertaken within 3 months of assessment date)
- Karnofsky Performance Status (see appendix A)
- laboratory tests to include the following:

i) complete blood count with differential including platelets

ii) serum chemistries to include electrolytes, creatinine, glucose, Ca, Mg, phosphate, AST, ALT, alkaline phosphatase, albumin and bilirubin (hereafter referred to as **serum chemistries**)

iii) flow cytometry panel (appendix G)

iv) serum or urine pregnancy test for women

v) HIV-1 ELISA and confirmatory test if not already available

vi) plasma storage for HIV load testing at central laboratory (appendix H)

vii) whole blood for PBMC processing/storage

#### 2. Visit 2

All results from pre-therapy visit 1 should be available.

- CBC, with differential
- flow cytometry panel
- randomize patient (conact Data Management Centre)
- plasma storage for HIV load testing
- whole blood for PBMC processing/storage

#### 3. Pre-cycle IL-2 (day 1/cycle 1) - Patients randomized to IL-2

This visit must occur within 96 hours of commencement of IL-2, for IL-2 therapy. The following tests must be completed and the results known to be in keeping with study eligibility criteria before the patient is treated with IL-2:

- physical examination, vital signs and Karnofsky Performance Status
- CBC, differential and chemistries
- urinalysis
- urine or serum pregnancy test for women of childbearing potential
- flow cytometry panel
- whole blood for PBMC processing/storage

### C. On study evaluations

Once randomized, patients will be treated with SC IL-2 (IL-2 treated) or no therapy (control). Follow-up and clinical assessments will be different for these patient groups. All on-study assessments are delineated in the following text and tables.

#### 1. IL-2 treated patients cycle 1, 2 and 3.

Patients should have cycle 1 IL-2 administered by a qualified health care professional. Patients should be taught, where possible, how to self administer therapy and should also be educated about the use of prophylactic medications for the management of side effects. The decision to allow the patient to self-administer IL-2 in subsequent cycles should be made by the investigational team.

**Table 3**

**CYCLE 1, 2 and 3 STUDY SCHEMA FOR IL-2 TREATED PATIENTS**

| Test/Assessment/Sample | Pre-cycle IL-2 (1) | D1 | D2 | D3 | D4 | D5 | D8(6)* | D29(6) |
| --- | --- | --- | --- | --- | --- | --- | --- | --- |
|  |  |  |  |  |  |  |  |  |
| SC IL-2 dosing |  | X | X | X | X | X |  |  |
| Toxicity/ adverse events(2) |  | X | X | X | X | X | X | X |
| Vital signs/ Karnofsky Performance Status | X |  |  |  |  |  |  | X |
| Physical examination(3) | X |  |  |  |  |  | X | X |
| CBC with differential and platelets(5) | X |  |  |  |  | X(4) |  | X |
| Serum chemistries(5) | X |  |  |  |  | X(4) |  | X |
| Pregnancy test-women only (5) | X |  |  |  |  |  |  |  |
| Flow cytometry | X |  |  |  |  |  |  | X |
| Plasma virology | X |  |  |  |  |  | X | X |
| Whole Blood for PBMC | X |  |  |  |  |  |  |  |

(1) All safety, virological and immunological laboratories must be performed within 96 hours prior to dosing.

(1) The results of all safety evaluations must be known before therapy may commence.

(2) Patients will document adverse experiences on diary cards on an ongoing basis.

(3) A complete physical exam will be performed prior to cycle 1. Thereafter physical exams will be symptom directed or as medically indicated.

(4) Can be obtained on day 4 or 5.

(5) Obtain during pre-therapy visit and immediately prior to dosing for each cycle.

(6) May be±5 days.

***These tests need be performed during administration of the first cycle of IL-2 only.**

Other laboratory testing consistent with patient safety, approved by the EthicsÕ Committee and discussed in the informed consent, may be performed on a site-specific basis.

#### 2. Control patients

In general these patients willrequire far less intensive monitoring than IL-2 treated patients. Nonetheless, it is important that control patients are reviewed at regular intervals to ensure continuity of follow-up and in an effort to curtail premature withdrawal from study.

Following assignment to this treatment arm, control patients should be reviewed as indicated in Table 4:

**Table 4**

**ANTIRETROVIRAL TREATED PATIENTS**

| Test/assessment/  sample | Week 0(1) | Week 8 (1) | Week 16 (1) | Week 24 (1) |
| --- | --- | --- | --- | --- |
|  |  |  |  |  |
| Vital signs/weight | X | X | X | X |
| History (2) | X | X | X | X |
| CBC/differential | X | X | X | X |
| Serum chemistries | X | X | X | X |
| Flow cytometry | X | X | X | X |
| Plasma virology | X | X | X | X |
| Whole Blood for PBMC | X | X | X | X |
| Pregnancy test- women only | X |  |  |  |

(1) These visits may take place ± 3 weeks

(2) Update treatment history; verification that no important events occurred

### D. Post-therapy evaluations

Post-therapy evaluations will be conducted on all patients. These evaluations must be completed in the time frame indicated by the following instructions:

- IL-2 treated patients who complete 3 cycles of therapy as described by this protocol should commence post-therapy evaluations no earlier than 8 calendar weeks after commencing the final cycle of IL-2.
- patients who have permanently discontinued IL-2 prematurely as a consequence of toxicity or any other reason, should commence post-therapy evaluations no sooner than 8 weeks after commencement of their most recent treatment cycle.
- control patients should commence post study evaluations no earlier than 24 weeks after entering study.

Post therapy evaluations consist of tests, procedures and samples as shown inTable 5:

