### 2. Sample size

Based on an estimate of within patient variability corresponding to a standard deviation of 150 cells/mm3 (data on file), and using a two-sided significance level of 5%, a total of 36 patients randomized in the ratio of 2 SC IL-2:1 control participant will give 80% power of detecting an increase in the SC IL-2 group of 150 cells/mm3 (175 cells/mm3 with 20% dropout).

Based upon an estimate of within patient variability corresponding to a standard deviation of 0.7 log copies/ml (Eron J et al, NEJM 1995; 333:1662-9), and using a two sided significance level of 5%, a total of 36 patients randomised in the ratio of 2 SC IL-2: 1 control participant will give 80% power to detect a 0.7 log copies/ml difference between treatment groups (0.8 log copies/ml with 20% dropout).

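### Sampling to week 24 is scheduled for controls but not for patients who stop or never start IL-2, so the intent-to-treat comparison rests on unequal, treatment-dependent windows

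*Protocol*

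**What the plan says.** All references are to the protocol.

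- **Endpoint and analysis (VIII.E.1, VIII.E.3).** The primary endpoint is the time-weighted mean change from baseline in CD4+ count and in plasma HIV-RNA. No averaging period is given. On the analysis set: "All efficacy data will be analyzed by the intent-to-treat principle".
- **Patients who stop IL-2 early (VIII.D).** They "should commence post-therapy evaluations no sooner than 8 weeks after commencement of their most recent treatment cycle".
- **Controls (VIII.D).** "control patients should commence post study evaluations no earlier than 24 weeks after entering study". Table 4 samples them at weeks 0, 8, 16 and 24, with flow cytometry and plasma virology each time.
- **IL-2 patients on treatment (Table 3).** Every visit is tied to a dosing cycle: pre-cycle, days 1 to 5, day 8 and day 29.
- **Closing visits (Table 5).** There are two, the second 2 to 14 days after the first. No later visit is scheduled.
- **After the protocol (VIII.F).** All patients should stay in follow-up once the protocol is completed, but no schedule is given, and continuing treatment belongs to another protocol.
- **Before the first dose (VIII.B.3).** This applies only to patients already randomised to IL-2: "The following tests must be completed and the results known to be in keeping with study eligibility criteria before the patient is treated with IL-2". Flow cytometry is on that list.

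**The concern.** An intent-to-treat comparison of a time-averaged outcome needs the outcome measured over the same period in every arm, whatever happened to treatment. Here the scheduled length of follow-up depends on how many cycles the patient started, and that can only shorten follow-up in the IL-2 arms. Stopping for toxicity or poor tolerance is plausibly related to the CD4+ and HIV-RNA course, so the lost follow-up is unlikely to be a random sample.

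The gap matters more than usual in this trial. The overview in section V says the protocol is meant to show that IL-2 is virologically neutral, and the introduction says there are no clinical data on IL-2 without antiretrovirals. The HIV-RNA course in the months after stopping is part of the answer, and it is not scheduled to be measured. An analysis plan can define windows or imputation, but it cannot supply samples that were never taken.

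**Working it through.** **1. The plan's own figure.** Section VIII.E.2 states that "a total of 36 patients randomized in the ratio of 2 SC IL-2:1 control participant will give 80% power" at a two-sided 5% level, for a difference of 150 cells/mm3 with SD 150, or 0.7 log copies/ml with SD 0.7. Both are differences of 1 SD.

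- Controls needed = (1.960 + 0.842)² × (1 + 1/2) = 11.8, rounded up to 12. With 24 on IL-2 the total is 36, as stated.
- Power at 24 v 12 is 80.7% by the normal approximation and 78.5% by the noncentral t.
- With 20% dropout (19.2 v 9.6) the detectable CD4+ difference is 166 (normal) or 172 (t), against the stated 175.

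The sample size is sound, and this point does not change it.

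**2. Last scheduled sample by treatment received.** A cycle is 8 weeks. The table assumes that cycles run on time and that the first closing visit is held at the earliest permitted date. Weeks run from the start of cycle 1 for dosed IL-2 patients and from study entry for controls.

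| Patient | First closing visit | Second closing visit, at latest | First closing visit as share of 24 weeks |
|---|---|---|---|
| IL-2, stops in cycle 1 | week 8 | week 10 | 33% |
| IL-2, stops in cycle 2 | week 16 | week 18 | 67% |
| IL-2, completes 3 cycles | week 24 | week 26 | 100% |
| Control | week 24 | week 26 | 100% |
| Randomised to IL-2, never dosed | none defined | none defined | 0% |

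The last IL-2 row follows because the early-stopping rule counts from the most recent cycle, Table 3 is tied to dosing, and Table 4 is for controls. No schedule fits a patient who never started.

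**3. Effect on the IL-2 mean.** The protocol gives no CD4+ course after stopping, so the following is assumed: a cycle-1 stopper is at +150 cells at week 8, and change is linear between 8-weekly values. The time-weighted mean is the area under the change curve divided by the window length.

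To week 8: (0 + 150)/2 = +75. To week 24:

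| Assumed change at weeks 8, 16, 24 | Area / 24 | Mean to week 24 | Truncated minus full |
|---|---|---|---|
| 150, 150, 150 | (600 + 1200 + 1200)/24 | +125 | -50 |
| 150, 75, 0 | (600 + 900 + 300)/24 | +75 | 0 |
| 150, 0, 0 | (600 + 600 + 0)/24 | +50 | +25 |
| 150, 0, -50 | (600 + 600 - 200)/24 | +42 | +33 |

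The shift in the IL-2 mean is the fraction stopping in cycle 1 times the last column:

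- 10% stopping: -5 to +3 cells
- 20% stopping (0.20 × 24 = 4.8, about 5 patients): -10 to +7 cells
- 40% stopping: -20 to +13 cells

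The 10% to 40% range is assumed. The 20% in VIII.E.2 is an overall dropout allowance, not a forecast of IL-2 discontinuation. For context, section II.B reports 7 of 18 patients (39%) discontinuing early in an earlier subcutaneous trial, on a different regimen of 13 four-week cycles.

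**4. Never-dosed patients.** Suppose 3 of 24 have no post-baseline data and drop out of the analysis. Noncentral-t power at 1 SD for 21 v 12 is 76%, against 78% for 24 v 12. The loss of power is small. What matters more is that patients are removed after randomisation from the IL-2 arms alone.

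**The case against.** The strongest reply has four parts.

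- **The comparison can still be run.** A time-weighted mean is averaged over whatever time was observed, so any randomised patient with a post-baseline sample has a value and can be analysed as randomised. This stands. A reader might infer that the intent-to-treat comparison cannot be carried out at all. For dosed patients the protocol does not support that; the fault is unequal windows. Only never-dosed patients lack a scheduled value.
- **The 8 weeks is a minimum.** Later closing visits are allowed, and section IX withdraws study therapy, not follow-up. This also stands, but permission is not a schedule: a site that follows the text exactly may stop sampling at week 10.
- **Some off-drug time is observed.** Dosing lasts five days of each eight-week cycle. Day 8 virology (first cycle), day 29 flow cytometry and virology, and both closing visits all fall after dosing. It would be wrong to say that nothing is seen after stopping; it is the later course that is missing.
- **The analysis plan may deal with unequal follow-up.** It may, but only by assumption, since the samples do not exist.

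A reader might also infer from VIII.B.3 that a CD4+ count below 350 after randomisation bars dosing, so that low re-testers are lost from the IL-2 arms only. The text does not settle this. Inclusion criterion (c) asks for one count before randomisation, and the notes to Table 3 require only that safety results be known before therapy. It is a wording conflict to reconcile, and no estimate of patients lost this way can be built on it.

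**Conclusion.** The point holds as a fault in data collection. Following the protocol exactly gives follow-up that depends on treatment received, in the IL-2 arms only, for an endpoint that is to be analysed by intent to treat. Patients who complete three cycles are not affected.

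The likely size is modest. At 20% stopping in cycle 1, the shift of -10 to +7 cells is at most about 7% of the 150-cell design difference (10/150). At 40%, -20 to +13 cells is at most about 13% (20/150). The direction is unknown, and the figures rest on the assumed +150 cells at week 8 and the four assumed courses after it. No figure can be given for HIV-RNA, because the protocol offers nothing on which to base its course after stopping; the loss there is of information that the trial is meant to provide. The case for acting is that missed samples cannot be recovered later and the remedy is cheap.

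**What to change.** 1. In VIII.D, state that every randomised patient who stops or never starts IL-2 has the Table 4 tests, including flow cytometry and plasma virology, at whichever of weeks 8, 16 and 24 from randomisation remain. Place the Table 5 visits after week 24 in all arms.
2. In VIII.E, state that the time-weighted mean is computed over the same 24-week window from randomisation for all patients.
3. Separately, reconcile VIII.B.3 with inclusion criterion (c) and the Table 3 note on safety results, so that it is clear whether a CD4+ count taken after randomisation bears on dosing. Which reading is intended is for the sponsor to say.

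**Cost.** A short amendment, plus two extra ordinary visits for a cycle-1 stopper (weeks 16 and 24), one for a cycle-2 stopper (week 24) and three for a never-dosed patient (weeks 8, 16 and 24). At 20% stopping, about five patients are involved. Sample size, alpha and power are unchanged.
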